## ***B. Involuntary Hospital Admission***

**Between 2012 and 2015, the practice of “involuntary treatment” in connection with cases of psychiatric crisis situations increased by 15 % in France**, i.e. a sharper increase than that of the active file for psychiatry, proportionately as well as in absolute value.

Approximately 92 000 people received involuntary care in 2015 (14). Among these, 79 000 were admitted to hospital (progression of 13%), making France one of the European countries that practices the most involuntary hospital admission. 16 000 people were placed in SDRE.

The average reported duration of medical programs (hospital and ambulatory) was between 12 and 22 months according to the legal modes, including 75 days in hospital (61 days without consent) (15).

During these involuntary hospital stays, the practice of seclusion, forbidden in other countries for ethical reasons (16), also increased: 8% of people involuntarily hospitalized in 2015 versus 4% in 2003 (14), which alerted organizations such as the French national observatory for places of deprivation of liberty, or the UN (Annex 2.2).

Concerning **involuntary hospital admission**, there are important national (14), European (17) and international (18) **disparities**:

- Quantitatively: average rate 177 /100 000 inhabitants in France, varying with a 1:6 ratio depending on the geographic department; rates between 6 and 218 / 100 000 inhabitants in Europe depending on the country;
- Qualitatively between countries: variations in terms of procedures, legal criteria (notions of danger, health needs), of the authority making the decision for coercion (medical/non medical) etc.

This **frequent and wide-spread use**, admittedly disparate, of coercion does not seem to be based on its efficiency, a systemic literature review on treatment without consent effectively found **little proof of the efficiency of these measures** in terms of state of health, social functioning, healthcare service use or of satisfaction (19).

**Negative effects** of involuntary hospital admission were identified in several studies, showing that these periods of deprivation of liberty are a very negative experience for the patient and can cause damage (20,21) that they have a negative impact on quality of life (22) and finally that the avoidance of future hospital admission has a negative effect on prognosis.

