## ***C. Number of subjects necessary and feasibility***

### **1. Number of subjects necessary**

Subjects included in the trial are people who were involuntarily admitted to hospital within the previous 12 months. According to data in French literature, the rate of involuntary hospital admission for patients suffering from psychotic disorders is 42.6% within 12 months after their previous admission(27).

Reducing these involuntary admissions by one third, i.e. 33%, would be a very significant reduction in terms of efficiency. This is a realistic hypothesis in the light of the most recent meta-analyses (59). We consider that 10% of participants will not reach experimental intervention and we estimate a 30% size effect. With these hypotheses, for an alpha risk of 2.5% (one-sided test) and 80% power, 182 subjects per group would be necessary. Over a 12-month period rate of lost to follow-up equal to 10% has been considered acceptable by the investigators involved in this project, especially with regards to the means scheduled to limit the number of people lost from sight.

Accordingly, the total number of subjects to include is 400 patients.

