### **2. Effectiveness Analysis**

#### **2.1. Primary Outcome Measures**

The analyses of the primary and secondary criteria will be performed on the intent-to-treat population. In addition, complementary per protocol analyses will be performed (that is comparison of persons who completed the intervention originally allocated).

The primary data will be summarized using frequencies. Comparisons between the two groups will be performed using chi-square or Fisher's exact tests for proportions. Multivariate analyses will be performed for the rate of admission using logistic regression. No adjustment will be carried out in the primary analysis.

Statistical analyses will be performed using SPSS Statistics for Windows, Version 20.0 (SPSS Inc. Chicago, IL, USA) or STATA 16 (StataCorp. 2019. Stata Statistical Software: Release 16. College Station, TX: StataCorp) LLC.

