## **4. Sensitivity Analyses**

As a sensitivity analysis, the regressions will be repeated including random effects for sites, and adjusted hazard/odds ratios will be provided based on potential un-balanced baseline characteristics or relevant covariates (such as diagnosis and age). Known or expected associations with the primary outcome variable in our study will be on the basis of previous evidence (e.g. previous publications) and/or on clinical grounds.

Sensitivity analysis will be carried out to address uncertainty around the cost-utility ratio. One-way sensitivity analysis and tornado diagram will be performed to identify thresholds for factors

influencing the ICUR. Probabilistic sensitivity analyses, using the non-parametric bootstrap method, will be carried out to generate mean expected ICURs and to determine whether uncertainty or variation in the data used affect the ICURs. In addition, cost-effectiveness acceptability curves will be drawn to represent decision uncertainty surrounding cost-utility estimates.

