## ***D. Limitation and justification***

### **1. Experimental plan**

The experimental plan retained is based on a randomized experimental diagram. In the light

of discussions about the generalization of the approach it is important to propose the trial diagram that brings the highest level of formal proof and the most recognized.

This plan's limit is linked to the potential contamination of the control group. The knowledge of this potential bias could have justified a cluster study or a Zelen design (96). The fact that the patients were randomly drawn by the investigators avoided this bias but introduced a new major limit which is the extreme diversity of investigator practices concerning involuntary hospital admission (professional practices linked to the place of work or the specialization), thus the need to greatly increase the number of subjects in the trial. Zelen design is a methodology that has never been used in France, and which presents the particularity of only informing the person which experimental arm they are in. Using this technique, which would reduce access to advance directives for the control group, from an ethical point of view this presents the particularity of privileging the principle of benevolence (limiting the feeling of "missing a chance") over the principle of autonomy (being informed of the entire research project). Given the central importance of the notion of autonomy in this research, classical randomization was chosen.

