## **3. Absence of pairing**

The implemented project does not offer pairing upon inclusion thus limiting comparability. The choice not to pair was based on the following observations:

- the factors of confusion to be taken into account have not yet been clearly defined;
- pairing according to variables such as age and gender would weigh down the procedure and limit inclusion;
- from an ethical point of view it seems difficult to propose pairing which requires prior randomization and which could lead to non inclusion in the project even though the population was solicited

The principle of prioritizing reality on the field, and the supposed or identified factors of confusion will be taken into account upon analysis as described in chapter VII. D. 3.

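### The primary test is explicitly unadjusted although the protocol describes large variation by place and practice; prespecified adjustment would recover a little power at almost no cost

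*Combined protocol and SAP*

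**What the plan says.** - **Primary analysis.** SAP section 2.1 (Primary Outcome Measures) specifies an intent-to-treat comparison of two proportions by chi-square or Fisher's exact test. It announces a multivariate logistic regression for the admission rate without listing covariates, and then states: "No adjustment will be carried out in the primary analysis".
- **Sensitivity analysis.** SAP section 4 says that "the regressions will be repeated including random effects for sites", and that "adjusted hazard/odds ratios will be provided based on potential un-balanced baseline characteristics or relevant covariates (such as diagnosis and age"). The next sentence ties known or expected associations with the primary outcome to earlier evidence or clinical grounds.
- **Variation.** Protocol I.B reports the French involuntary admission rate as "varying with a 1:6 ratio depending on the geographic department". Protocol VIII.D.1 (Experimental plan) speaks of "the extreme diversity of investigator practices concerning involuntary hospital admission", which it links to workplace and specialization.
- **Confounders.** Protocol VIII.D.3 (Absence of pairing) says that confounding factors are not yet clearly defined, and then that "the supposed or identified factors of confusion will be taken into account upon analysis as described in chapter VII. D. 3".
- **Allocation.** Protocol VI.A.1 describes a list drawn up before inclusion starts. The calendar mentions lists in the plural. Neither mentions stratification by site.
- **Baseline data.** Diagnosis is checked at eligibility. Age is among the baseline socio-demographic items. Data on use of care are marked at baseline in the assessment table.

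**The concern.** The authors treat place and practice as important enough to rule out cluster allocation without a much larger sample, yet leave them out of the primary model. If site and patient characteristics predict readmission, an unadjusted comparison leaves explainable variation in the error term. That costs power in a trial with little to spare.

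A second, smaller issue concerns the adjusted model. Diagnosis and age are given only as examples, and apparent imbalance at baseline is one permitted reason to include a covariate. The covariates can therefore be settled after the data are seen. Imbalance is also a poor criterion, because the gain from adjustment comes from how strongly a covariate predicts the outcome. The one place that promises to explain how confounders are handled refers to chapter VII, which is the calendar and has no section D.3.

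**Working it through.** **Inputs from protocol VI.C.1.** The control risk is given as "the rate of involuntary hospital admission for patients suffering from psychotic disorders is 42.6% within 12 months after their previous admission". The reduction is stated first as 33% and then as 30%, after allowing for 10% who do not receive the intervention. The size is given as "for an alpha risk of 2.5% (one-sided test) and 80% power, 182 subjects per group would be necessary". Loss is 10% and the total is 400, so 360 are analysed, or 180 per arm.

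**Step 1: reproduce the plan's figure.** For two proportions with pooled variance under the null,

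n = [1.960·√(2·p̄·(1−p̄)) + 0.842·√(p1(1−p1) + p2(1−p2))]² / (p1 − p2)²

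- 33% reduction: p2 = 0.426 × 0.67 = 0.2854, p̄ = 0.3557, n = (1.327 + 0.564)² / 0.1406² ≈ 181. This matches 182.
- 30% reduction: p2 = 0.426 × 0.70 = 0.2982, p̄ = 0.3621, n = (1.332 + 0.567)² / 0.1278² ≈ 221. This does not match.

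The sample size therefore rests on an unadjusted two-proportion test, consistent with the SAP, and on the 33% effect.

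**Step 2: power without adjustment, 30% effect, 180 per arm.**

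Φ[(0.1278 × √180 − 1.332) / 0.674] = Φ(0.568) = 71.5%

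Under the 33% effect it is 79.8%.

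**Step 3: approximate gain.** If baseline covariates explain a share R² of outcome variance, replace n by n/(1−R²). The R² values are assumptions.

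| R² | Effective n per arm | Power |
|---|---|---|
| 0 | 180 | 71.5% |
| 5% | 189 | 73.7% |
| 10% | 200 | 76.0% |
| 15% | 212 | 78.3% |

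At R² = 10% this equals 360/0.9 = 400 analysed, that is, 40 more patients. That figure depends wholly on the assumed R².

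**Step 4: simulation.** 360 patients were analysed in three sites of 135, 135 and 90 (150/150/100 less 10%), with 42.6% versus 29.8%, a one-sided 2.5% test and 4,000 runs per cell. A pooled z test was compared with logistic regression on arm, site and one binary covariate present in 40%. That covariate was modelled as a higher prior-admission count and stands in for patient-level prognostic information. All strengths are assumed. Each cell gives unadjusted → adjusted power.

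| Covariate odds ratio; site shifts (logit) | Simple list | Stratified by site |
|---|---|---|
| 1; 0 | 71.9% → 71.7% | 71.7% → 71.6% |
| 1.5; ±0.2 | 71.6% → 72.2% | 72.6% → 72.9% |
| 2; ±0.3 | 70.8% → 72.5% | 72.5% → 73.7% |
| 2; ±0.5 | 71.2% → 73.0% | 72.9% → 74.8% |
| 3; ±0.5 | 71.6% → 75.2% | 71.6% → 75.6% |
| 4; ±0.7 | 72.7% → 78.5% | 71.3% → 77.5% |

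The gain runs from none to about 6 points. A test on the standardised risk difference gave power within half a point of the logistic test. Type I error was 1.9% to 2.9% unadjusted and 2.3% to 3.1% adjusted, against a nominal 2.5% with simulation error of about 0.25 point. Neither test shows material inflation.

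**The case against.** The strongest reply is that an unadjusted, prespecified chi-square is a sound primary test in a randomized trial and matches the method behind the sample size. Chance imbalance between sites is already covered by its error rate. All of this stands.

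Several stronger readings are tempting, and the documents do not support them.

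- **That the adjusted model selects covariates by imbalance alone.** SAP section 4 also admits relevant covariates, names diagnosis and age, and appeals to earlier evidence or clinical grounds. Imbalance is one of two routes.
- **That prior admissions are known to drive the outcome and are already recorded.** Nowhere is their number said to predict the outcome. At least one in the prior year is an inclusion criterion, so only the count can vary. Protocol VI.A.2 lists number, duration and type of hospital stays, but does not name a prior-year count of involuntary admissions.
- **That a site random effect is plainly wrong because there are three sites.** Three cities would be too few to estimate a variance well. But the version table calls added hospitals recruitment sites, protocol III.F describes seven hospitals (two in Lyon, three in Marseille, two in Paris), and the qualitative section counts four sites. With seven units a random effect is defensible. The SAP does not say which level it means.
- **That the 1:6 ratio measures site differences in this trial.** It concerns population rates across French departments, not readmission in this cohort.
- **That the SAP breaks a promise.** Protocol VIII.D.3 promises to account for confounders in the analysis, not in the primary test, and SAP sections 2.1 and 4 go some way towards that.

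**Conclusion.** The point holds as an efficiency improvement. Leaving out adjustment forgoes about 0 to 6 points of power, starting from 71.5% under the 30% effect with 180 analysed per arm. The size rests on assumed prognostic strengths: under 1 point if they are weak, about 4 points with a covariate odds ratio of 3 and site shifts of ±0.5, and about 6 only if they are strong. A reader might infer that the primary result would be biased or its error rate inflated; neither is so. Nor does adjustment settle the conflict between the 33% and 30% effects in protocol VI.C.1, which is the main reason that power is 71.5% and not about 80%.

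The open covariate list, the imbalance route and the dead cross-reference are real but affect supportive analyses only. Label: cheap improvement.

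**What to change.** 1. Make the primary analysis a logistic regression of any involuntary admission within 12 months on arm, site, diagnosis and age. Enter site as a fixed effect and state its level, city or hospital. Add the prior-year count of involuntary admissions if the baseline care-use form captures it. Close the list.
2. Report the standardised (marginal) risk difference and risk ratio with 95% confidence intervals.
3. Keep the unadjusted chi-square as a supportive analysis.
4. Delete unbalanced baseline characteristics as a reason for adjustment in SAP section 4.
5. Replace the reference to chapter VII.D.3 in protocol VIII.D.3 with the SAP section that handles covariates.
6. State whether the randomization list is stratified by site. Site belongs in the model either way.

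**Cost.** No extra patients are needed, and no extra data for site, diagnosis and age. The small downside is a model-based primary test in place of a two-by-two test. The SAP is dated January 2019 and recorded as unchanged during the study, so this would be a dated amendment made before outcomes by arm are seen. If that point has passed, the adjusted analysis should be reported as supportive.

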## **2.2. Secondary Outcome Measures**

The data will be summarized using the mean, median, standard deviation and range of quantitative data. Mean score values will be compared with the Student t test or the Mann–Whitney U test. Secondary outcome scores will be analysed using generalized linear models with a normal distribution with an identity or log link.

The cost-utility analysis will be carried out according to the recommendations of the French Health Authorities (HAS). The final result of the economic analysis is the incremental cost-utility ratio (ICUR) that is the ratio of added cost to added effectiveness, which expresses the additional costs per additional QALY. Univariate sensitivity analyses will be carried out by varying health and cost parameters. As recommended by the HAS, the statistical uncertainty surrounding the ICUR will be captured by a probabilistic analysis, using, among others, simulation methods such as non-parametric bootstrap methods.

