#### a. Results criteria

##### Criteria related to health

- Anamnestic data and personal medical history;
- Data related to recourse to care and economical data (given in detail in the chapter Economic analysis § D. 3.4)
  - number, duration and type of somatic, psychiatric and addictology hospital stays,
  - number of visits to the emergency department,
  - number of medical consultations,
  - number of sick leaves and reduction of professional activity
- Data related to the therapeutic alliance between the patient and their psychiatrist:
  - Assessed using the questionnaire 4-Point Alliance Self Report (4-PAS), French scale validated showing good psychometric properties with alpha equal to 0.91 (Misdrahi, 2009)(78).
- Data related to mental health assessed from:
  - Recovery, assessed using the self-administered questionnaire Recovery Assessment Scale (RAS) (76,77). Recovery is defined as living a satisfying life despite constraint linked to the mental disease, by analogy with recovery from physical disability, where the person can overcome impairments due to their physical illness and accomplish most of their life goals if they receive adequate assistance and makes the necessary arrangements(76). This scale, validated in a population suffering from severe mental

disorders, demonstrated satisfying psychometric properties(77). It is made up of 24 items, exploring 5 dimensions: self-confidence, capacity to ask for help, life goals, confidence in others, no domination by symptoms. Answers are rated on a Likert scale with 5 points. A global score is obtained as well as sub-scores for the 5 dimensions. Recovery will be assessed using the Recovery Assessment Scale (RAS) at M0, M6 and M12. It has been validated in French.

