## **3. Data collection periods**

Individual case report forms have been developed especially for this trial; they are articulated around the three assessment periods described in the following chapter: initial assessment and follow-up visits at 6 and 12 months.

Data will be collected at a place of the patient's choice.

Data will be manually entered into a laptop dedicated to this use, using software specifically developed for the trial.

The following table summarizes the contents and the frequency of assessments for the two groups of subjects included in the trial.

|                                                                            | Eligibility
Inclusion
Init. Ass. | 6 months | 12 months |
|----------------------------------------------------------------------------|----------------------------------------|----------|-----------|
| Informed consent, check inclusion/exclusion criteria:                      |                                        |          |           |
| admissibility questionnaire                                                | x                               |          |           |
| Sociodemographic characteristics                                           | x                               |          |           |
| Anamnestic data & personal medical history                                 | x                               |          |           |
| Data related to mental health:                                             |                                        |          |           |
| CGI                                                                        | x                               |          | x  |
| Recovery: RAS                                                              | x                               | x | x  |
| Therapeutic alliance: 4-PAS                                                | x                               | x | x  |
| Insight: SUMS                                                              | x                               | x | x  |
| Empowerment: ES                                                            | x                               | x | x  |
| Quality of life: S-QOL                                                     | x                               | x | x  |

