## 6. Handling of Missing Data

Missing data will be handled where possible using multiple imputations or other method according to the type of missing data.

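### The main analysis of the secondary scores specifies no baseline adjustment, target visit or repeated-measures handling, and so may give up precision that the collected data would provide

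*Combined protocol and SAP*

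**What the plan says.** The protocol's data collection section (VI.A.3) sets three assessment times: "initial assessment and follow-up visits at 6 and 12 months". The section on results criteria says the same for one scale, "Recovery will be assessed using the Recovery Assessment Scale (RAS) at M0, M6 and M12", and the schedule table gives the same three times for 4-PAS, SUMS, ES, S-QOL and CSQ-8. CGI is marked at baseline and 12 months only.

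The SAP (VI.E) covers the analysis of these scores in two sentences of section 2.2:

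- On the simple comparison of arms: "Mean score values will be compared with the Student t test or the" (the alternative named there is the Mann–Whitney test).
- On modelling: "Secondary outcome scores will be analysed using generalized linear models with a normal distribution with an identity or log link".

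Neither sentence names a visit, a baseline covariate, a visit term or a correlation between visits. No ANCOVA, mixed model or GEE is named anywhere in the SAP.

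Three other SAP statements bear on the point:

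- Section 2.1 puts the secondary criteria on the intention-to-treat population. Its statement "No adjustment will be carried out in the primary analysis" stands under the primary outcome.
- Section 4 says that "the regressions will be repeated including random effects for sites, and adjusted hazard/odds ratios will be provided based on potential un-balanced baseline characteristics". It also allows other covariates, with diagnosis and age as examples.
- Section 6 says "Missing data will be handled where possible using multiple imputations or other method according to the type of missing data".

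**The concern.** Scores such as alliance, recovery and empowerment usually correlate within a patient over time. A t test or Mann–Whitney test on 12-month scores cannot use that correlation. Part of the between-patient variation that the baseline score would explain stays in the standard error, and confidence intervals are wider than the data require.

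The protocol's objectives (II.A.1) describe these outcomes as improvements, yet the stated comparison is of mean score values. Because visit, test, link and covariates are all open, each scale can be analysed in several defensible ways. The t test and the Mann–Whitney test also answer different questions, and the SAP gives no rule for choosing between them.

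At stake is the trial's ability to detect modest effects on the outcomes that the intervention should move most directly, using data that will be collected anyway.

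**Working it through.** **The plan's own figure.** The documents give no SD, effect size, power or correlation for any secondary score. The only sample-size statement concerns the primary outcome: "for an alpha risk of 2.5% (one-sided test) and 80% power, 182 subjects per group would be necessary". Two proportions, 42.6% against 42.6% × 0.67 = 28.5%, pooled variance, no continuity correction, give 181 per group, which agrees with 182. (The 30% effect also stated in VI.C.1 gives 221. That is a separate matter and does not enter below.)

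**Inputs.**

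- Total of 400 and 10% loss to follow-up (VI.C.1): 400 × 0.90 / 2 = 180 per group.
- Two-sided 5% and 80% power for the scores: assumed. Multiplier 1.96 + 0.84 = 2.80.
- r, the baseline-to-12-month correlation: assumed, 0.3 to 0.8.

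**Formulas**, in units of the 12-month SD, against an unadjusted 12-month comparison:

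- Variance ratio, adjusted to unadjusted: 1 − r².
- Share of information given up: r².
- Detectable difference, unadjusted: 2.80 × √(2/180) = 0.295 SD.
- Detectable difference, adjusted: 0.295 × √(1 − r²).
- Unadjusted group size with the same precision: 180 / (1 − r²).

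| r (assumed) | 1 − r² | Information given up | Detectable difference, adjusted | Equivalent unadjusted n per group |
|---|---|---|---|---|
| 0.3 | 0.91 | 9% | 0.282 SD | 198 |
| 0.4 | 0.84 | 16% | 0.271 SD | 214 |
| 0.5 | 0.75 | 25% | 0.256 SD | 240 |
| 0.6 | 0.64 | 36% | 0.236 SD | 281 |
| 0.7 | 0.51 | 49% | 0.211 SD | 353 |
| 0.8 | 0.36 | 64% | 0.177 SD | 500 |

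**What the 6-month score adds.** Generalized least squares was applied to all three visits with a common baseline mean, separate arm means at 6 and 12 months, and equal correlation r between visits. With complete data the 12-month variance ratios are 0.75, 0.64 and 0.51 at r = 0.5, 0.6 and 0.7, identical to adjustment for baseline alone. The whole gain in the table therefore comes from baseline.

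**If change scores were compared instead.** Their variance relative to the unadjusted 12-month score is 2(1 − r). The ratio of ANCOVA to change is (1 − r²) / [2(1 − r)] = (1 + r)/2, that is 0.75, 0.80 and 0.85 at r = 0.5, 0.6 and 0.7. The saving is then 25%, 20% and 15%.

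**The case against.** The strongest reply is that the SAP is silent on adjustment and does not exclude it. A normal identity-link model with baseline as a covariate is ANCOVA, so the model sentence could already cover the fix. The no-adjustment statement belongs to the primary outcome, and section 4 foresees adjusted regressions. This stands as far as it goes: a reader might infer that the plan rules baseline out, and it does not. But section 4 is a sensitivity analysis and names hazard and odds ratios, which are not mean differences. The protocol's promise to handle confounders at analysis (VIII.D.3) points to a section of chapter VII, which is the calendar. The t test or Mann–Whitney test remains a stated comparison and has no place for a baseline covariate.

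Three other inferences go too far:

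- *That 25–49% is a known loss.* It depends on an assumed r and on an unadjusted 12-month comparator, and the SAP fixes neither.
- *That the unused 6-month scores cause it.* With complete data they do not.
- *That patients seen at 6 but not 12 months contribute nothing.* The intention-to-treat population and the planned multiple imputation could bring them in. The imputation variables are not stated, so this is unsettled rather than excluded.

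A further objection concerns the remedy. Under VI.B, patients are told their arm at inclusion, and the initial assessment may follow up to one month later, though before the intervention starts. The protocol (IX.A.2) itself expects that controls may feel they have lost a chance. Self-reported baseline scores could therefore react to allocation, and adjusting for them assumes that they do not. This is a genuine but limited drawback, and it does not cancel the gain.

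**Conclusion.** The point holds as a gap in specification and a likely loss of precision in the secondary scores. If an unadjusted 12-month comparison is what is run, it gives up about 25% to 49% of the information at r = 0.5 to 0.7, and 9% to 64% over r = 0.3 to 0.8. Against change scores the saving from adjustment is 25% to 15% over r = 0.5 to 0.7. These figures rest on assumed correlations, two-sided 5% testing, 180 per group and complete 12-month data.

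A reader might also take this as a threat to validity. The documents do not support that: randomisation protects the unadjusted complete-data comparison, and chance baseline imbalance is already reflected in its standard error. The sample size rests on the primary outcome alone, which this point does not touch. The change is worth making because it is nearly free, and it does not call the trial's main conclusion into question.

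**What to change.** In SAP section 2.2, replace the t test or Mann–Whitney comparison as the main analysis of the scores:

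- **Target.** The baseline-adjusted mean difference between arms at 12 months, with 95% CI, for each scale.
- **Model.** Either a mixed model of the 6- and 12-month scores on arm, visit, arm by visit, baseline score and site, or ANCOVA of the 12-month score on arm, baseline score and site. Choose one in advance. A stated visit and covariate list would close the gap in either case.
- **CGI severity.** ANCOVA, since it is scored at baseline and 12 months only. The CGI improvement item already rates change since inclusion and has no baseline to adjust for.
- **Population and missing data.** Keep the intention-to-treat population of section 2.1. State in section 6 that any multiple imputation includes the baseline and 6-month scores, so that randomised patients without a follow-up score are not dropped by the choice of model.
- **Baseline timing.** Where possible, complete the baseline scores before allocation is disclosed. Report the unadjusted 12-month difference as a sensitivity analysis.

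The cost is SAP wording and a little programming in the software already named. No new data or visits are needed. Moving the baseline scores ahead of disclosure changes the order of steps at inclusion and may lengthen that meeting.
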